#### Health economic analysis

A health economic analysis is performed to determine the efficiency of the intervention. To this end, cost-effectiveness analyses and cost-utility analyses are conducted. The output of the health economic evaluation is the total and incremental costs and effects (time to heal, health-related quality of life, other effects) of the intervention and control group. Using an incremental cost-effectiveness ratio (ICER), the incremental costs and effects are weighed against one another to quantify the cost-effectiveness of the intervention in comparison to treatment as usual. Only costs directly attributable to the treatment of the VLU are counted in the analysis.

In line with the IQWIG’s guidelines (CITE), the health economic analysis is conducted from the perspective of German statutory health insurances and their insured persons, meaning that only costs and effects incurred on the side of the health insurances and the patients are accounted for in the analyses [20]. Resource consumption and costs of inpatient care and outpatient care, drug prescriptions, remedies, and medical aids attributable to the treatment of VLU are counted in the analyses. The number of ambulatory care visits (surgery, dermatology, internal medicine, other specialist care), number of hospitalizations and days spent in inpatient care, days on sick leave, and travel costs will be collected using a healthcare utilization questionnaire. The medical care delivered or prescribed for participating patients will be collected using practice internal documentation. Here, the number of GP visits for wound treatment, prescribed home care and long-term care, prescribed remedies, and medical aids related to the VLU, as well as drug prescriptions and wound dressings will be recorded. The time horizon of the analysis is 12 months beginning from baseline (T0). Effects are measured at three points in time for both the intervention and the control group (T0, T1, T2), while costs are measured at one point in time, retrospectively at the end of each participant’s study trajectory (T2).

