### Intervention

Ulcus Cruris Care is a multifaceted intervention aiming to implement a disease management concept for outpatient treatment of VLU patients in GP practices. The intervention comprises four major components shown in Table 3.

**Table 3 Tab3:** The intervention components in “Ulcus Cruris Care”

Components of the intervention “Ulcus Cruris Care”	
1	Online training and e-learning courses for GP practices
2	Standard operating procedures for VLU treatment
3	Software support for VLU disease management
4	E-learning courses and printable information for patient education

*VLU* venous leg ulcer

Participating GPs and medical assistants will receive joint online training via webinar according to a synchronous concept comprising 2 teaching units of 45 min each. In addition, asynchronous target-group-specific e-learning courses are provided via an online platform (https://welearn.academy). Online training and e-learning are mandatory to be completed before inclusion of the first patient and will be tracked via documentation and within the online platform. The didactic interventions are designed to support the implementation of a standardized disease management process for VLU patients in GP practices. Under GP supervision, medical assistants are intended to take a central role in wound treatment and patient monitoring and education. Central learning content comprises wound assessment, compression therapy, local wound therapy, and patient education. As a secondary learning objective, practical skills of correctly applying and assessing a compression bandage are to be conveyed. An online video demonstrating the application of compression bandages is integrated in the e-learning course, which is online available at any time. Online training and e-learning courses were designed and reviewed by physicians from the department for general practice and the department for dermatology at the University Hospital of Heidelberg.

To support standardized treatment, the practices are provided with standard operating procedures based on current guidelines for medical compression therapy, wound cleaning and local wound treatment for VLU.

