## Discussion

The UCC trial is the first study to evaluate a disease management concept for the treatment of VLU. The Ulcus Cruris Care program was developed to support standardized evidence-based and patient-centered treatment of VLU in GP practices. Its intervention elements are intended to enhance the knowledge and practical skills of caregivers, support standardized treatment of VLU, and promote informed and active participation of patients. As an inherent objective, Ulcus Cruris Care is intended to promote the application of compression therapy by supporting knowledge on the caregiver side and patient adherence, which are the main barriers to its use [13, 15, 23].

With regard to limitations, it has to be mentioned that allocation concealment for participating patients is not feasible. Patients will not be informed about the allocation of their treating GP practice; however, patients in the intervention group receive access for e-learning and print-based information. Furthermore, patient recruitment may be affected by the ongoing COVID-19 pandemic. However, to ensure its feasibility, timelines and recruitment aims have been adapted according to our experiences in currently ongoing studies.

The UCC trial will help to evaluate whether the Ulcus Cruris Care intervention may lead to faster wound healing, a higher health-related quality of life and a lower use of medical resources. If the intervention turns out to have a positive impact on assessed outcomes, comprehensive implementation in primary care may be considered. Furthermore, if successful, the concept of Ulcus Cruris Care may serve as a role model for further disease management concepts for chronic wound treatment.

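### As written, the cost analysis leaves out training, e-learning, the VLU software module and printed material, so the ICER and the cost comparison describe the programme as if supplied free of charge

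*Protocol article*

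**What the plan says.** The Health economic analysis section gives the purpose of the ICER as "to quantify the cost-effectiveness of the intervention in comparison to treatment as usual". It then limits the costs:

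- By type: "Only costs directly attributable to the treatment of the VLU are counted in the analysis".
- By payer: "only costs and effects incurred on the side of the health insurances and the patients are accounted for in the analyses", which is the perspective of statutory health insurers and their insured.
- By time: 12 months, starting at each patient's baseline (T0).

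The items follow: "Resource consumption and costs of inpatient care and outpatient care, drug prescriptions, remedies, and medical aids attributable to the treatment of VLU are counted". A patient questionnaire adds specialist visits, hospital stays, sick leave and travel. Practice records add "the number of GP visits for wound treatment, prescribed home care and long-term care", together with remedies, aids, drugs and dressings.

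The Intervention section describes the programme: "joint online training via webinar according to a synchronous concept comprising 2 teaching units of 45 min each", e-learning for staff, standard operating procedures, a VLU module in existing case-management software, and patient e-learning and print material. Practice training and e-learning must be completed before a practice includes its first patient. According to the Control section, control practices receive none of this.

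The Statistical analysis section forms the ICER from mean costs of care per arm and also plans a non-inferiority comparison of those costs. The Discussion says that after a positive result "comprehensive implementation in primary care may be considered".

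**The concern.** The quantity is presented as the cost-effectiveness of the intervention, yet the cost rule admits none of the inputs that distinguish the intervention arm. Those inputs are used in one arm only, so leaving them out does not cancel in the difference between arms. A finding that care costs no more, or less, in the intervention arm could then arise because the programme was priced at zero. A payer reading the ICER or the cost comparison would have no sign of this from its label. This rests on restrictive wording (only these costs, only these payers), not on silence that a fuller plan might fill.

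**Working it through.** The document states no unit cost, ICER or cost margin, so there is no figure to reproduce. The check has three parts.

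**1. Is each programme component admitted by the cost rule?**

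| Component | Treatment cost of the VLU incurred by insurer or patient? | Within 12 months from T0? | In the item list? |
|---|---|---|---|
| Practice webinar and staff e-learning | Not as described | No, precedes the first patient | No |
| VLU software module | Not as described | In use after T0 | No |
| Patient e-learning and print material | Not as described | Yes | No |
| Additional medical-assistant case management | Unclear | Yes | No item for staff time |
| Extra GP wound visits, home care, dressings | Yes | Yes | Yes |

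The last row is captured at least in part; the first three are not. Neither the ICER formula nor the planned sensitivity analyses mention a programme cost.

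**2. Direction.** Let P > 0 be the programme cost per intervention patient and 0 the cost in control. Let ΔC be incremental cost including the programme, and ΔE the difference in effects, coded so that higher is better.

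- Planned numerator = ΔC − P.
- If ΔE > 0, planned ICER = (ΔC − P)/ΔE, which is too low by P/ΔE.
- At any threshold λ, net benefit λΔE − ΔC is overstated by P.
- If the planned analysis shows a saving of S per patient, the programme saves money overall only if P < S.
- The mean cost difference in the non-inferiority comparison shifts by the same P.

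**3. Volume.** The Sample size section gives 63 patients per arm in 21 practices, with 25 practices to be recruited:

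- 63/21 = 3.0 patients per practice
- 63/25 = 2.52 patients per practice

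The only programme input with a stated quantity is the webinar: 2 × 45 min = 1.5 h. Assuming one GP and one medical assistant attend, that is 2 × 1.5 = 3 staff-hours per practice:

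- 3/2.52 = 1.19 h per patient
- 3/3 = 1.0 h per patient
- 3/20 = 0.15 h per patient at 20 VLU patients a year, the most an eligible practice may have under Table 1

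For a total programme cost C per practice, P = C divided by patients per practice. C is not in the document. The range below is assumed purely to show scale, as is ΔE = 0.02 QALY.

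| Assumed C (EUR) | P at 2.52 | P at 3.0 | P at 20 | ICER shift at 2.52 and 0.02 QALY |
|---|---|---|---|---|
| 250 | 99 | 83 | 12.5 | about 5,000 per QALY |
| 1,000 | 397 | 333 | 50 | about 19,800 per QALY |
| 4,000 | 1,587 | 1,333 | 200 | about 79,400 per QALY |

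The last column is P/0.02; for example 396.8/0.02 = 19,840. Across this range the answer depends heavily on C and on the volume over which it is spread. That is why both should be shown.

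**The case against.** The strongest reply is that a declared perspective is not a bias. The section states whose costs count and cites a guideline; costs borne by a developer or a practice fall outside by definition. This stands: the perspective is legitimate and the planned analysis need not be replaced. It does not settle what the result may be called, because an ICER labelled as that of the intervention will be read as including it.

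Several stronger readings are tempting and are not supported:

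- **The project or the practices bear the programme cost.** The article does not say who pays, in the trial or later. If insurers paid, the payer rule would no longer exclude the cost, but the treatment-only rule and the item list still would.
- **No delivery cost is counted.** GP wound visits, home and long-term care and dressings are recorded, so some extra activity caused by the programme does enter.
- **All medical-assistant time and all software is an omitted cost of one arm.** Table 1 requires both arms to have an assistant routinely involved in wound care and to meet the software's IT requirements. Only additional assistant time and the VLU module are specific to the programme.
- **The ICER's stated purpose is roll-out.** The stated purpose is efficiency. The Discussion ties possible implementation to a positive impact on assessed outcomes, not to the ICER alone, and the process evaluation examines implementation effort separately.

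It is also fair that materiality is not shown. The one input that can be quantified is small, 20 patients a year is an eligibility ceiling and not a roll-out volume, and costing detail may sit in an analysis plan that is not shown. A later plan could add a programme-cost scenario; as the article stands, its wording points the other way.

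**Conclusion.** The point holds in a limited form. As written, the ICER and the cost non-inferiority comparison exclude training, e-learning, the VLU software module and printed material, while part of the additional care the programme triggers is counted. Read as the cost-effectiveness of the programme, both favour the intervention by P per patient, and the ICER by P/ΔE if the intervention is more effective. The direction follows for any positive programme cost. The size cannot be derived, and the euro and QALY figures above are assumptions. A reader might infer that a cost-saving result would be false; the document does not support that, since P may be small against any saving. The primary outcome is unaffected.

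**What to change.** Keep the planned analysis and state, wherever its results appear, that programme costs are excluded. Add one scenario, for both the ICER and the cost comparison, with a per-patient programme cost in the intervention arm:

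- training time, platform, VLU software module and printed material, from the sponsor's own budget;
- an assumed range for any additional medical-assistant case-management time over usual care, since staff time is not among the recorded items.

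Spread fixed costs once over trial volume (2.52 to 3 patients per practice) and once over a stated, assumed roll-out volume. Base any cost-saving or implementation statement on the version that includes programme costs.

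The cost is one more scenario from figures the sponsor should largely hold, and a somewhat less favourable result. No change to patient data collection, sample size or the primary analysis is needed.

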### Statistical methods

#### Sample size

The sample size calculation is based on the primary outcome “time to complete wound healing (“time-to-heal”)”. Assumptions are based on the literature: a healing rate after 12 weeks of 60% is assumed in the standard care (control group) [23] and, based on clinical studies on patient-centered interventions, of 80% [24] in the intervention group. With a significance level of *α* = 0.05, an assumed drop-out rate of 20%, and the assumption of exponentially distributed healing curves, a sample size of *n* = 55 patients per study arm is needed to achieve a power of 80% when applying a log-rank test in the classic two-group comparison. In order to take the cluster structure of the data into account (patients in doctors’ practices), the sample size is further adjusted by a design effect of 1.1, which is calculated from a cluster size of *n* = 3 patients per practice and a conservative intra-cluster correlation coefficient (ICC) of 0.05. This results in a total sample size to be recruited for the study of *n* = 126 patients (*n* = 63 per group) in *n* = 42 practices (*n* = 21 per group). In addition, in order to prevent possible drop-outs or recruitment bottlenecks among the GP practices, the target number of practices to be recruited is increased to *n* = 50 (*n* = 25 per group). This will increase the power in the study, as a larger number of clusters has a positive effect on the design effect. The sample size planning was carried out using PASS software.

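### The questionnaire-based cost items are collected only once, at 12 months, although on the plan's own healing assumptions most open-ulcer time falls before the existing 3-month visit.

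*Protocol article*

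**What the plan says.** The section on the health economic analysis (Protocol article) sets a 12-month horizon from baseline and counts only costs attributable to the venous leg ulcer. Effects are taken at T0, T1 (3 months) and T2 (12 months), "while costs are measured at one point in time, retrospectively at the end of each" participant's trajectory, that is, at T2.

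Two cost sources are named:

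- **Questionnaire.** Specialist outpatient visits, hospitalizations and inpatient days, "days on sick leave, and travel costs will be collected using a healthcare utilization questionnaire".
- **Practice records.** "The medical care delivered or prescribed for participating patients will be collected using practice internal documentation". These cover "the number of GP visits for wound treatment, prescribed home care and long-term care, prescribed remedies, and medical aids related to the VLU", and also drug prescriptions and wound dressings.

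The section on statistical analysis plans a non-inferiority analysis of costs and an ICER whose numerator is the difference in mean costs. The section on sample size assumes 60% (control) and 80% (intervention) healed at 12 weeks, exponential healing curves, and "an assumed drop-out rate of 20" per cent.

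**The concern.** For the questionnaire items no other source is named, so whatever is not recalled at T2 is lost. The plan expects most patients to have healed by T1. Much of the ulcer-related care would then lie 9 to 12 months back when it is asked about, and reports of visits, travel and sick days tend to fade over such a span. A patient who leaves before T2 is never asked.

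This is a decision about data collection, and a later analysis plan cannot recover what was not asked at T1. At stake are the cost difference, the ICER and the non-inferiority analysis of costs. The primary outcome, time to healing, is not touched.

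**Working it through.** **Inputs.** Healed at 12 weeks 60% and 80%, exponential healing, 20% drop-out, 126 patients (section on sample size). T1 at 3 months, taken as week 13, and T2 at 12 months, taken as week 52 (Table 4).

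**Step 1: hazards per week.** Control: −ln(0.40)/12 = 0.0764. Intervention: −ln(0.20)/12 = 0.1341. Hazard ratio 1.756.

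**Step 2: do these inputs reproduce the plan's own figure?** For two-sided 5% and 80% power, the Schoenfeld formula gives 99 events and the Freedman formula 105. I assume 52 weeks of follow-up and 20% drop-out spread exponentially over them; the mean event probability is then 0.950. Per arm: 99/(2 × 0.950) = 52.1, so 53; 105/(2 × 0.950) = 55.3, so 56. The stated 55 lies between. The design effect is 1 + (3 − 1) × 0.05 = 1.1, and 55 × 1.1 = 60.5, so 61, rounded up to 21 practices × 3 = 63. The inputs are being read as intended.

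**Step 3: open-ulcer time.** Expected open-ulcer weeks up to week t are (1 − e^(−λt))/λ.

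| | Weeks 0–13 | Weeks 0–52 | Share before T1 |
|---|---|---|---|
| Control | 8.24 | 12.85 | 64% |
| Intervention | 6.15 | 7.45 | 83% |
| Difference | 2.09 | 5.40 | 39% |

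With T1 at week 12 the shares are 61% and 80%. Most ulcer time precedes T1 in both arms, but 61% of the between-arm difference arises after it.

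**Step 4: effect of under-recall.** The documents give no recall rate, so let a fraction f of pre-T1 cost be forgotten in both arms and all later cost be recalled.

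- *Cost follows ulcer time.* The apparent saving is 5.40 − 2.09f ulcer-weeks: 5.19 at f = 0.1, 4.77 at f = 0.3 and 4.35 at f = 0.5. It shrinks by about 4%, 12% and 19%.
- *True totals on these items equal in both arms, timed as in Step 3.* The reported share is 1 − 0.64f in control and 1 − 0.83f in intervention. At f = 0.1, 0.3 and 0.5 this is 94% against 92%, 81% against 75%, and 68% against 59%. The intervention then looks about 2%, 7% and 14% cheaper on these items.

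The two cases point in opposite directions.

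**Step 5: missing questionnaires.** 0.20 × 126 = 25.2, so up to about 25 patients without these items and about 101 with them, if every drop-out occurs before T2.

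**The case against.** The strongest reply is that much of the ulcer care is not recalled at all. GP wound visits, home and long-term care, remedies, medical aids, drugs and dressings come from practice records. This stands. A reader might infer that the whole cost comparison rests on distant recall, but the text does not support that. The article gives no cost shares, so the weight of the questionnaire items is unknown, although they include inpatient days.

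A reader might also infer that drop-outs supply no cost data and that the analysis is confined to completers. Neither is stated. Practice records may exist for a patient who misses T2, and the handling of missing costs belongs in the statistical analysis plan. The drop-out rate is given without its timing, so 25 is an upper figure.

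A third tempting reading is that the bias favours the intervention because a larger share of its ulcer time lies far back. That confuses the proportion lost with the amount lost. The ICER uses a difference in mean costs, and before T1 the control arm has more ulcer time (8.24 against 6.15 weeks). If cost follows ulcer time, equal forgetting removes more from control and works against the intervention.

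Finally, 64% and 83% are shares of ulcer time, not of cost. They ignore recurrences, which the trial follows to month 12 and which would move ulcer time later. The article also does not say who completes the questionnaire or what aids are used. All of this limits how far the size can be pinned down. It does not remove the single retrospective measurement.

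**Conclusion.** The point holds for the questionnaire items: specialist visits, hospitalizations and inpatient days, sick leave and travel. They are collected once, with recall of up to 12 months, while about 64% (control) and 83% (intervention) of expected first-year open-ulcer time falls before T1. Under-recall can distort the cost difference, the ICER and the cost non-inferiority analysis. Its direction depends on the true costs, and its size depends on a recall rate and cost shares that the documents do not give. Up to about 25 of 126 patients could lack these items.

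The figures rest on the plan's healing assumptions, first episodes only, cost proportional to ulcer time, and all drop-out before T2. This is a weakness in a stated design choice of an accompanying analysis. It is not a contradiction in the document, but it is worth correcting because it is cheap to correct and cannot be repaired after data collection.

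**What to change.** Give the same utilization questionnaire twice: at T1 for months 0–3 and at T2 for months 3–12. The longest look-back falls from 12 months to 9, and for the first period, where most ulcer time is expected, to 3. Patients lost after T1 keep their first-period costs, which the missing-data analysis can use.

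The cost is one extra short form per patient at a visit that already takes place and at which EQ-5D-5L, PHQ-9 and PACIC-5A are already completed. A second extraction of the practice documentation is not needed, because those data do not depend on recall.

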#### Process evaluation

The process evaluation of the UCC trial aims to explore factors contributing to or hindering successful implementation of the “Ulcus Cruris Care” intervention and its working mechanisms using a mixed-methods approach. At the beginning of the trial, the participating healthcare providers of both study arms will be surveyed by a questionnaire to collect demographics and descriptive data on the GP practices. A knowledge check of all participating caregivers will be performed using a standardized multiple-choice quiz comprising a total of 10 questions on disease, pathophysiology, diagnostics, and treatment of venous leg ulcers. At the end of the intervention period in the trial, a process evaluation questionnaire using decision questions, 5-point Likert scales, and free-text responses will be addressed to all participating caregivers and patients of the intervention arm to assess intervention fidelity, reach among patients, acceptance of intervention components, implementation effort, and potential sustainability and transferability to other settings. In addition, semi-structured interviews of a total of 35 persons are planned, including 10 GPs, 10 medical assistants, and 10 patients in the intervention arm as well as 5 regional stakeholders from health insurance and professional associations. Interviews will be conducted once practices have gained initial experience with the intervention and after completion of practice training and treatment of at least 2 patients within the study. Evaluation of the interviews and free-text answers from the questionnaires will be carried out in an inductive-deductive procedure using a framework analysis according to Gale et al. [21]. The Consolidated Framework for Implementation Research (CFIR) will be applied to categorize influencing factors during implementation [22]. Data will be organized and analyzed using the MAXQDA software.

